## Discussion

### Potential impact and significance of the study

The neck-specific exercise program used in this trial is currently a widely discussed component of the rehabilitation for patients with neck pain. It has been recommended due to its efficacy in decreasing the intensity of neck pain and improving the quality of life [17, 18]. However, to date, this study would be a pioneer in verifying the efficacy of this protocol in patients with migraine. We believe that individuals may benefit from this protocol, as patients with migraine have several musculoskeletal disorders. If the effect of this exercise program for patients with migraine is similar to that observed in patients with neck pain, it would be possible to reduce the impact of migraine by reducing the frequency and the intensity of migraine attacks, which is the main goal of the multi-professional team in the management of migraine [7].

### Strengths and weaknesses of the study

Strengths of the study include the design and the novelty of investigating whether a neck-specific strengthening exercise program might reduce the frequency and intensity of migraine attacks. The gold-standard treatment for migraine is pharmacological. However, manual techniques and therapeutic exercises have shown satisfactory results in reducing migraine attacks and improving quality of life. We recognize that the application of an exercise program alone is a limitation of this study, because it may not represent common clinical practice. However, from a scientific perspective, the effects of this protocol should be specifically determined before combining it with other interventions.

We can cite as other limitations: no long-term follow-up, attention bias from the differences between groups in the time spent with a therapist, long home exercise assignments, only partial blinding of participants (they can distinguish treatments, but they are blinded to sham ultrasound), the estimates of the mean and standard deviation used in the sample size calculation came from a different study population, and adverse events will not be collected.

Finally, although we will attempt to make the number of meetings the same when inserting the sham group with ultrasound, patients who will receive this placebo may have the feeling of greater attention because they will receive a type of hands on therapy. In addition, patients in the sham group may have a greater perception of improvement than the intervention group. However, implementing a placebo group that received another type of exercise would also be controversial because the effects of non-specific exercises on migraine are already known.

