**Methods:**

A two-armed, parallel-groups randomized controlled trial with 3 months of follow-up will be conducted. 42 individuals, both genders, aged between 18 and 55 years old with a medical diagnosis of migraine will be included. The intervention group will perform a protocol consisting of exercises for strengthening the muscles of the cervical spine. Participants within the sham ultrasound group will receive detuned ultrasound therapy in the upper trapezius muscle. Both groups will receive a weekly session for 8 weeks. The efficacy of each intervention will be measured by the frequency and intensity of migraine at a 3-months follow-up.

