## Introduction

Migraine is classified as a chronic [1] and disabling disease [2] characterized by recurrent headache attacks lasting from 4 to 72 h, with a unilateral location and pulsating quality. Migraine attacks range from a moderate to severe intensity that increases with daily routine, physical activity, and can be accompanied by nausea and/or photophobia and phonophobia [3]. In addition to these features, neck pain is quite common [4] and is associated with a worse prognosis for the disease [5].

Pharmacologic treatment is currently the gold standard for migraine management [6]. However, a multidisciplinary approach is also recommended [7] and manual techniques and therapeutic exercises may be valuable adjunct treatments as they help to reduce symptoms, prevent migraine attacks [8], and result in a relevant clinical reduction of the frequency and intensity of migraine attacks while increasing patient satisfaction with the treatment [9].

Among the various manual technique interventions, aerobic exercises in combination with physical and psychological interventions result in a reduction in the duration of migraine attacks [8]. It is known that aerobic exercises were as effective in reducing the frequency of migraine attacks as standard pharmacological treatment with topiramate and tricyclics [10]. In addition, manual therapy interventions targeting the craniocervical region have also demonstrated beneficial results, such as improvement in the quality of life, reduction of pain intensity, reduction in related disability, and a reduced frequency of migraine attacks [11–14]. However, despite evidence showing that different manual techniques and therapeutic exercises in the craniocervical region are effective in migraine management [8–14], to date, the effects of cervical muscle strengthening exercises on this population are unknown [15].

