### Interventions

This study will be performed to compare a neck-strengthening exercise protocol with a sham ultrasound group in migraine subjects. In both groups, there will be a combination of home stretching exercises. The interventions in both groups will last for 2 months. After completion of treatment, patients of both groups will be followed up by phone at 1, 2, and 3 months.

Intervention group (IG): the 8-week exercise program to be used in this study will be based on the protocol described by Falla et al. [28], which consists of specific exercises to strengthen the flexor and extensors muscles of the neck. Participants will receive instructions and guidance from a trained therapist for 30 min once a week. The protocol consists of two stages:
*Stage 1:* The first stage, of 6-week duration, will focus on incremental craniocervical flexion in a relaxed, supine position and craniocervical extension, flexion, and rotation in a prone-on-elbows position while maintaining the cervical spine in a neutral position (Fig. 2) [28]. The initial proposal for the deep flexors and extensors of the cervical spine will be 2 sets of 10 repetitions. However, for the deep flexor muscles, the movement should be initially sustained for 10 s. If the participant cannot perform the targeted program, the number of sets, repetitions, and time of sustentation (for the deep flexors) will be redefined. According to the tolerance of the patient, the sets, repetitions, and time of sustentation will be increased weekly [28].*Stage 2:* The second stage, of 2-week duration, consists of both flexor and extensor exercises with higher load, using head weight as the load [28]. A neck flexion associated with a head flexion will be performed with the participant in the supine position, removing the head from the stretcher. For the extension exercise, while performing the neck extension the patient will be instructed to maintain the cervical spine in the neutral position, and the body in the position of 4 supports (Fig. 3). Each of the exercises will be for 3 sets of 15 repetitions at a time over the course of 2 weeks [28].

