**Fig. 3 Fig3:**
[figure not shown]
Second stage of neck-specific exercise program

Participants will be instructed to perform the same exercises at home, twice a day, for 10–20 min a day. They will receive a guideline book containing a neck-specific exercise program, including neck muscle stretching exercises.

Sham ultrasound group (USG): participants in this group will have meetings once a week for 8 weeks. The application of disconnected of therapeutic ultrasound (US) will be performed bilaterally in the middle portion of the upper trapezius. The application time will be around 9 min for each side, totaling approximately 20–25 min per session. Participants will also receive a guideline book, containing only cervical spine stretching exercises.

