### Process variable

All volunteers will meet weekly with the responsible therapist. During all meetings, the therapist will ask, and note, if the volunteers: are doing the home care. If volunteers get additional care, the therapist will be informed and this information will be noted. As well as the use of non-prescribed medications.

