### Contribution to the physical therapy profession

We believe that the current trial will bring innovative and unprecedented results to improve the management of individuals with migraine. If we observe that the neck-specific exercise program is effective in reducing the frequency and intensity of migraine attacks, professionals will be offered a low-cost and easily applicable therapeutic option.

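### Adverse events are deliberately left unrecorded despite weekly questioning in both arms, so tolerability of the exercise programme will have no event-level data

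*Protocol article*

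**What the plan says.** The decision stands in the Discussion, under Strengths and weaknesses of the study, as one item in a list of limitations: "adverse events will not be collected". No other section provides for recording harms.

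The contact schedule is regular and the same in both arms:

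- Abstract, Methods: "Both groups will receive a weekly session for 8 weeks".
- Process variable: "All volunteers will meet weekly with the responsible therapist", and "During all meetings, the therapist will ask, and note, if the volunteers: are doing the home care". Other care received and medication taken without prescription are noted too. Harms are not among the questions.
- Interventions: after treatment, both groups are contacted by phone at 1, 2 and 3 months.

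On exposure in the exercise arm, the Interventions section says of the first stage: "According to the tolerance of the patient, the sets, repetitions, and time of sustentation will be increased weekly". A second stage with higher load follows. Of home practice it says: "Participants will be instructed to perform the same exercises at home, twice a day, for 10–20 min a day".

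On the conclusion to be drawn if frequency and intensity fall, Contribution to the physical therapy profession says: "professionals will be offered a low-cost and easily applicable therapeutic option". The Conclusion of the Abstract says much the same.

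**The concern.** This is a stated decision, so it is not a detail that a condensed article leaves to a fuller document. Naming it as a limitation discloses the gap without closing it, and the gap is avoidable because the contacts at which harms could be asked about already exist.

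The Introduction says that the effects of cervical strengthening in migraine are unknown, and the Discussion presents the trial as the first of this protocol in such patients. No earlier experience of harms in this population is offered as a reason not to ask. The plan also foresees that some participants will not manage the programme, since sets, repetitions and holding times are to be redefined for them, but it does not make intolerance an outcome.

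At stake is the harms side of the report. If the programme reduces migraine, it would be offered to practice without any account of what individual participants experienced while doing it. Events not asked about at the time cannot be reliably recovered later.

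**Working it through.** **1. The plan's own figure, to fix the denominators.** Inputs from Sample size: α = 0.025, power 80%, difference 3.3 days, SD 3.1, loss 20%. With a two-sided normal approximation:

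n = 2 × (2.2414 + 0.8416)² × (3.1/3.3)² = 2 × 9.505 × 0.8825 = 16.8 per group; 16.8/0.8 = 20.97, so 21.

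This reproduces the stated 21. For intensity (1.52, SD 1.37), the same formula gives 15.4, and 15.4/0.8 = 19.3, so 20, again as stated. The sample size is not in question. The denominators are 21 exercised participants, or about 17 after the planned loss (21 × 0.8 = 16.8).

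**2. What the planned outcomes can and cannot show.**

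| Information | Source in the plan | Available? |
|---|---|---|
| Average change in headache days and intensity by arm | Outcomes (diary) | Yes |
| Average change in neck pain and disability by arm | Outcomes; Questionnaires | Yes |
| An individual event and its seriousness | None | No |
| Relation of an event to a session or to home exercise | None | No |
| Events outside the outcomes, e.g. dizziness | None | No |

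The diary is analysed as days of pain per month and as an average intensity, so a participant who was harmed is merged into a group mean.

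**3. What recording would add.** If no event of a given type is seen in n participants, the one-sided 95% upper limit for its rate is 1 − 0.05^(1/n):

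- n = 21: 1 − 0.05^(1/21) = 0.133
- n = 17: 1 − 0.05^(1/17) = 0.162

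The chance of seeing at least one event at a true rate p is 1 − (1 − p)^n. The rates are assumptions, since the document gives none:

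| Assumed rate | n = 21 | n = 17 |
|---|---|---|
| 1% | 0.19 | 0.16 |
| 5% | 0.66 | 0.58 |
| 10% | 0.89 | 0.83 |
| 20% | 0.99 | 0.98 |

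Common harms would probably appear; rare ones probably would not.

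**4. A formal comparison of arms.** For assumed rates of 5% and 20%, a two-sided 5% test of two proportions has power of about 31% with 21 per arm and 26% with 17. Any gain is therefore descriptive.

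**5. Contacts available.** 8 weekly meetings + 3 phone contacts = 11 per participant, and 11 × 42 = 462 at most in the whole trial. No new visit is needed.

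**The case against.** The strongest reply is that the authors disclose the point, that it contradicts nothing in the plan, and that the primary comparison is intact. All of that is true. It limits the weight of the point but does not answer it, because the limitation is chosen and cheap to remove.

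Several stronger readings are tempting, and the document does not support them.

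- *That the trial could not detect any harm from exercise.* Headache days and intensity are primary outcomes and neck pain is a secondary one, in both arms. An average worsening could be seen. What is lost is event-level information.
- *That the Introduction concedes that exercise provokes attacks.* It says: "Migraine attacks range from a moderate to severe intensity that increases with daily routine, physical activity". That concerns how intense an attack is, not what sets it off, and the same section reports that therapeutic exercise helps to prevent attacks.
- *That nobody watches over participants.* A trained therapist guides the exercises, adapts them for those who cannot perform them and progresses them by tolerance. This is some oversight, although it yields no harms data.
- *That withdrawals due to harm could not be told from other losses.* The article does not say that reasons for withdrawal go unrecorded, and a condensed article may leave this to the full protocol. Nor would recording adverse events by itself repair the handling of missing data.
- *That the authors claim safety.* They claim low cost and easy application, conditional on efficacy. Only the tolerability side of applicability is touched.

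There is also a fair objection to how harms would be recorded. The therapist who treats both arms necessarily knows the allocation, so a weekly record would be unblinded. The article does not say who makes the phone calls; if it is the blinded data collector, talk of exercise sessions could reveal the arm. Questions about reactions to a session make no sense once sessions have ended. These points shape the remedy and do not remove the need for it.

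**Conclusion.** The concern holds in a limited form. By stated decision, individual harms, their seriousness, their relation to treatment and events outside the outcome list will go unrecorded, although weekly contacts in both arms and three phone contacts would allow it. The tolerability part of the conclusion on applicability would then have no data behind it. The efficacy comparison, the significance level and the sample size are untouched.

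In size, the loss is of descriptive information: upper limits of about 13% (21 observed) to 16% (17 observed) for event types never seen, and a good chance of noticing harms at a rate of 10% or more. Without collection, no such statement can be made. These figures rest on independent participants, complete questioning of those counted, and the assumed event rates shown.

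**What to change.** Replace the statement in Strengths and weaknesses with a provision in Methods that adverse events are collected in both arms:

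- At each weekly meeting: the same open question in both arms and a short fixed list (for example headache, new or worse neck pain, dizziness, other), including symptoms after the session or after home exercises.
- At each of the three phone contacts: an open question on new or worse symptoms, put by someone other than the blinded assessor or worded so that the answer does not reveal allocation.
- For every event: severity, and whether it led to withdrawal.
- Reporting: counts of participants and events by arm, descriptive only. State that the weekly record is made by a therapist who knows the allocation, and that zero events of a type exclude only rates above about 13% to 16%.
- Until such data exist, word the conclusion on applicability so that it does not imply tolerability.

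The cost is one added item on a form already completed weekly, a short question at calls already planned, some reporting work and possibly an ethics notification. No visit, staff member or sample size changes, and the interventions stay as they are.

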### Contribution to the physical therapy profession

We believe that the current trial will bring innovative and unprecedented results to improve the management of individuals with migraine. If we observe that the neck-specific exercise program is effective in reducing the frequency and intensity of migraine attacks, professionals will be offered a low-cost and easily applicable therapeutic option.

## Data Availability

The datasets used and/or analysed during the current study are available from the corresponding author on reasonable request.
